#### Blood pressure

2.6.2

Blood pressure will be measured by a digital blood pressure monitor (Panasonic, Hikone, Japan). Participants will be lying supine and the measurements taken from the right arm. Three measurements 1 min apart will be obtained, and a mean taken.

#### Blood analysis

2.6.3

Blood samples will be obtained by venepuncture from an antecubital vein and 10 ml of blood will be taken. The sample will be placed into two EDTA tubes. The samples will be centrifuged at 4000 *g* for 10 min at 4°C. The plasma will be frozen in aliquots on dry ice prior to being frozen at −80°C until further analysis.

Plasma LDL‐C, HDL‐C, total cholesterol, triglyceride, ApoB, glucose and NEFA concentrations will be analysed via spectrophotometry using a Daytona Rx (Randox, Crumlin, County Antrim, UK). Insulin and CRP concentrations will be analysed using commercially available enzyme‐linked immunosorbent assay kits. If funding is available, lipidomic analysis will be done by nuclear magnetic resonance spectroscopy to determine the full lipid profile, which will include glycoprotein acetyls.

#### Blood glucose control

2.6.4

A continual glucose monitor (Freestyle Libre Pro iQ, Abbott Diabetes Care, Maidenhead, UK) will be fitted to the posterior aspect of the upper arm during baseline testing and worn for 14 days. A second monitor will be fitted 14 days prior to the final laboratory visit and will be removed on arrival at the laboratory. Data from the glucose monitors at week 1, week 2, week 11 and week 12 will be used to determine 14‐day coefficient of variation for blood glucose concentration as the primary analysis, as well as 14‐day mean and standard deviation of blood glucose concentration, and 14‐day mean amplitude of glycaemic excursions for blood glucose (Battelino et al., 2019).

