## Abstract

Cardiovascular disease (CVD) is the leading cause of death worldwide. Physical activity interventions improve almost all modifiable CVD risk factors, but the effect of physical activity on low density lipoprotein cholesterol (LDL‐C) is uncertain. This may be due to lack of research on the feeding status in which the physical activity is performed. The aim of this study is to investigate the effect of fasted versus fed exercise on LDL‐C concentrations in males and females. One hundred healthy participants, equal males and females, aged between 25 and 60 years will be recruited and will undergo a home‐based 12‐week exercise intervention. After baseline testing, participants will be randomized to a fasted exercise (exercise after an 8‐h fast) or fed exercise (exercise 90–180 min after ingestion of 1 g kg^−1^ CHO) group and will perform 50 min of moderate intensity exercise (e.g., 95% heart rate of lactate threshold 1) three times a week either before or after a high carbohydrate (1 g kg^−1^) meal. Participants will visit the laboratory again at week 4 and week 12 and measurements will be taken for body composition, resting blood pressure, fasting blood glucose, lipid profiles and systemic inflammation, lactate threshold, and 14‐day blood glucose control.

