### Study design

2.1

This study was approved by Bristol Research and Ethics Committee (22/SW/0061) and registered on ClinicalTrials.gov (ID NCT05279014). The study design will be a randomized, parallel study of 100 inactive males (*n* = 50) and females (*n* = 50) conducted over a 2‐year period (Figure 1). The intervention will be a 12‐week exercise programme in which participants will be randomized to exercise either in a fasted state (FASTED‐EX) or in a fed state (FED‐EX). Participants in the FASTED‐EX group will perform exercise sessions at least 8 h after the last meal to ensure they are in a fasted state (Ruge et al., 2009) and eat a carbohydrate‐based meal after exercise. Participants in the FED‐EX group will perform the exercise sessions 90–180 min after the carbohydrate‐based meal. The sessions will be completed in either the morning or the evening and participants will be stratified for randomisation based on their preference of exercise timing. The participants will attend the physiology laboratory at the University of Bath on three occasions, at baseline, week 4 and upon completion of the intervention (i.e., week 12). The study will be conducted in accordance with the *Declaration of Helsinki* (Figure 1).

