#### Exercise intervention

2.6.7

Following baseline testing, participants will undertake a 12‐week home based exercise intervention. Participants will perform 50 min of moderate intensity exercise, 3 days per week, as per current UK physical activity guidelines (Davies et al., 2019). The participant will be able to decide where to complete the exercise sessions. The exercise will be at a low‐to‐moderate intensity (e.g., 95% heart rate of LT1) to ensure greatest fat oxidation in the fasted group (Achten & Jeukendrup, 2004) and will likely represent a brisk walk for most participants. The exercise can be done either outside or on an indoor treadmill. The exercise sessions can be completed on any day of the week but participants will be asked to take at least one rest day between sessions. Participants will be asked to perform at least two out of three of the weekly sessions at the time of day stated during randomisation. The exercise intensity will be prescribed based on heart rate and will equate to 95% of LT1 heart rate. Participants will be provided with a Wahoo activity monitor (Wahoo Fitness LLC, Atlanta, Georgia) and will be asked to monitor their heart rate on the phone application during the exercise sessions. The FASTED‐EX group will perform the exercise after an 8 h fast and will ingest a high carbohydrate meal (1 g kg^−1^ body weight) after each session. The FED‐EX group will exercise 90–180 min after the same high carbohydrate meal. Participants will be able to choose the meal from a predetermined list with prescribed portion sizes ensuring the meal is similar to food they would habitually eat. The meal list includes, but is not limited to, a bowl of cereal and semi‐skimmed milk, toast with jam, bagel and low fat cream cheese, and beans on toast. Participants will be emailed every 2 weeks with their energy expenditure and heart rate during the exercise sessions to encourage compliance with the study protocol. If the intensity of exercise in which LT1 is achieved changes from week 1 to week 4, the prescribed heart rate of the exercise sessions will be amended to ensure the same relative intensity of exercise is undertaken throughout the remaining study period.

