### Statistical analysis

2.7

Statistical analysis will be performed on Prism 9 version 9.4.1 (GrahPad Software, San Diego, CA, USA). An intention‐to‐treat analysis will be performed on data of all participants who are randomized. Data will be assessed for normal distribution by inspection of residual plots. Difference between groups at weeks 4 and 12 will be assessed by ANCOVA adjusting for stratification factors, sex and baseline measurements for the whole sample (Bland & Altman, 2015). Additional exploratory analysis will be performed adjusting for change in body mass from baseline for the whole sample and subgroup analysis on males and females separately for all outcomes. Differences between sex at weeks 4 and 12 will be assessed by a two‐way ANCOVA. Statistical significance will be defined as *P* ≤ 0.05.

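### The first glucose-monitor window overlaps the randomised intervention, so it cannot serve as baseline for the weeks 11–12 comparison

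*Protocol article*

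**What the plan says.** All references are to the protocol article.

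- **Sensor timing (2.6.4 Blood glucose control).** The first monitor is fitted "during baseline testing and worn for 14 days". For the second, "A second monitor will be fitted 14 days prior to the final laboratory visit". The article then states that "Data from the glucose monitors at week 1, week 2, week 11 and week 12 will be used to determine" the 14-day metrics, with the coefficient of variation as the main one.
- **Randomisation (Abstract).** "After baseline testing, participants will be randomized to a fasted exercise" or fed exercise group.
- **Start of the programme (2.6.7 Exercise intervention).** "Following baseline testing, participants will undertake a" 12-week home programme. "Participants will perform 50 min of moderate intensity exercise, 3 days per week".
- **Week numbering (2.1 Study design).** Laboratory visits take place "at baseline, week 4 and upon completion of the intervention (i.e., week 12".
- **Outcome (2.5 Outcome measures).** Glucose control over 14 days is a tertiary outcome, listed among the change outcomes and assigned to weeks 11 and 12.
- **Model (2.7 Statistical analysis).** Groups are compared by "ANCOVA adjusting for stratification factors, sex and baseline measurements for the whole sample".

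**The concern.** A baseline covariate in a randomised comparison must be measured before allocation can act on it. Here the sensor is put on at the baseline visit and records the two weeks after it, which are the first two weeks of assigned exercise. From the first session the arms differ in whether a 1 g/kg carbohydrate meal comes before or after exercise, so an effect on glucose variability within those two weeks is plausible.

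If that window is the covariate, or the origin of a change score, any effect already present is partly or wholly removed from the weeks 11–12 comparison. A real difference in glucose control could then be reported as small or absent. Section 1 (Introduction) gives the lack of any assessment of glucose control over the study period in the preliminary work as part of the background to this trial.

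**Working it through.** **Step 1: timeline.**

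| Event | When | Section |
|---|---|---|
| First sensor on | baseline visit | 2.6.4 |
| Randomisation | after baseline testing | Abstract |
| Programme starts | after baseline testing; no run-in described | 2.6.7 |
| First sensor data | 14 days from fitting, labelled weeks 1 and 2 | 2.6.4 |
| Week 12 | completion of the 12-week programme | 2.1 |

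Since week 12 is the end of a 12-week programme, weeks 1–2 are its first two weeks. If they were an untreated run-in, week 12 would be only the tenth week of exercise. The visit spacing agrees. Section 2.6 keeps follow-up visits in the same menstrual stage on a 28-day cycle. Visits 28 and 84 days after baseline are 1 and 3 cycles later. With a 14-day delay after the baseline visit they would fall at days 42 and 98, or 1.5 and 3.5 cycles.

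Assigned sessions in the first window: 3 × 2 = 6, out of 3 × 12 = 36 (17%). Six is an upper figure, because the day of the first session is not given.

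**Step 2: what can act as baseline.** The article describes two monitor windows. The second is the outcome. A change, or a baseline monitor value for the ANCOVA, can only come from the first.

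**Step 3: effect of adjusting for it.** The article gives no figure for the glucose outcome, so there is nothing of its own to reproduce; its power statement concerns LDL-C. Let D be the true effect at weeks 11–12, f·D the effect already present in weeks 1–2, and r the within-arm correlation of the two windows, with equal SDs so that the ANCOVA slope is r. Then:

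- ANCOVA group coefficient = D − r·(f·D) = D(1 − f·r)
- change-score difference = D − f·D = D(1 − f)

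The article gives neither f nor r; the values below are assumptions.

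| f | ANCOVA, r = 0.5 | ANCOVA, r = 0.8 | Change score |
|---|---|---|---|
| 0 | 100% | 100% | 100% |
| 0.25 | 1 − 0.125 = 88% | 1 − 0.20 = 80% | 75% |
| 0.5 | 1 − 0.25 = 75% | 1 − 0.40 = 60% | 50% |
| 1 | 1 − 0.5 = 50% | 1 − 0.8 = 20% | 0% |

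A negative f (an early effect in the opposite direction) makes both factors exceed 1. For example, f = −0.25 with r = 0.6 gives 1 + 0.15 = 115% under ANCOVA.

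**Step 4: simulation check.** With 4000 simulated trials of 40 per arm, D = 0.5 SD, r = 0.6 and f = 0.5, the mean ANCOVA estimate was 0.354. The formula gives 0.5 × (1 − 0.3) = 0.35.

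**Step 5: illustration of power.** Take D = 0.5 SD (assumed), r = 0.6 and n = 40 per arm (the 80 completers of section 2.8). The standard error is √[(1 − r²)(2/n + (fD)²/(2n − 2))].

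- f = 0: 0.50/0.179 = 2.80, power 80%
- f = 0.5: 0.35/0.180 = 1.94, power 49%
- f = 1: 0.20/0.185 = 1.08, power 19%

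**The case against.** The strongest reply is that the article never calls weeks 1–2 a baseline. Section 2.7 refers to baseline measurements in general and does not name the monitor window as a covariate. The two windows could be meant as early and late on-treatment glucose. The design figure is not available here, and a full protocol or analysis plan might settle the covariate.

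Part of this stands. That weeks 1–2 is the baseline is an inference, though a strong one, because the article offers no other window. The early-versus-late reading does not remove the problem: the change would then measure adaptation during training rather than the effect of fasted versus fed exercise. A later analysis plan can drop the covariate, but it cannot supply monitor data from before treatment.

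Three stronger readings are tempting, and the article does not support them:

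- **That the bias is always toward no effect.** This needs an early effect in the same direction as the late one.
- **That most of the effect is lost.** The lowest figures need the whole late effect to be present within two weeks, and f and r are both assumed.
- **That the trial's main result is compromised.** The LDL-C baseline is a blood sample taken at the visit that precedes randomisation.

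**Conclusion.** Wrong as written, for one tertiary outcome. The article fixes the sensor timing, the weeks used, a change outcome and baseline adjustment, and together these leave only an on-treatment window to act as the monitor baseline. The timeline is firm apart from the unstated day of the first session. The use of weeks 1–2 as covariate or origin of change is inferred.

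The size depends on two unknowns. With r between 0.5 and 0.8, an early effect one quarter of the late one costs ANCOVA 12–20% of the true difference, and one half costs 25–40%. A change score loses the full fraction f. If allocation has no effect on glucose in weeks 1–2, nothing is lost. The point should be corrected, but it does not bear on the primary analysis.

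**What to change.** In sections 2.5 and 2.7, state that the monitor metrics at weeks 11–12 are compared directly between arms, with weeks 1–2 monitor data used neither as a covariate nor as the origin of change. Adjust for fasting plasma glucose from the baseline visit, the stratification factors and sex. Report weeks 1–2 as an early on-treatment outcome.

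This is a change of wording only. The cost is some precision, because fasting glucose is likely to predict the monitor metrics less well than an earlier monitor period would. Section 2.5 also makes secondary outcomes, fasting glucose among them, subject to funding. If that assay were not run, the adjustment would rest on the stratification factors and sex alone.

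Moving the first sensor to before randomisation would give a true baseline, but at a higher cost. Fitted at the present baseline visit with a 14-day wait, it would put later visits half a cycle out of menstrual phase. Fitted earlier, it may need an extra visit. If introduced part-way through recruitment, it would mix two definitions of baseline in one trial.

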#### Microbiome

2.6.5

Participants will be provided with stool sample kits and asked to provide samples prior to baseline testing and end point testing. The samples will be stored and sent for analysis of gut microbiome species enrichment if funding allows. Analysis will be controlled for self‐reported antibiotic use.

#### Exercise testing

2.6.6

Participants will be fitted with a digital heart rate monitor (Polar Electro Oy, Kempele, Finland) and perform a submaximal treadmill exercise test to determine lactate threshold. A baseline blood lactate concentration will be measured by finger prick blood analysis using Lactate Pro. The test will commence at 2.5 km h^−1^ at a gradient of 0% and consist of 6 × 4‐min incremental stages. During the first three stages the speed will be increased by 1 km h^−1^ up to 4.5 km h^−1^. The speed will then remain the same and the gradient will be increased by 4% for the remaining three stages until completion. Blood lactate concentrations will be taken during the last minute of each stage. Heart rate and rating of perceived exertion (Borg, 1970) will also be recorded during the last minute of each stage. LT1 will be determined at the point where blood lactate concentration rises by 0.5 mmol l^−1^ above resting concentrations.

#### Exercise intervention

2.6.7

Following baseline testing, participants will undertake a 12‐week home based exercise intervention. Participants will perform 50 min of moderate intensity exercise, 3 days per week, as per current UK physical activity guidelines (Davies et al., 2019). The participant will be able to decide where to complete the exercise sessions. The exercise will be at a low‐to‐moderate intensity (e.g., 95% heart rate of LT1) to ensure greatest fat oxidation in the fasted group (Achten & Jeukendrup, 2004) and will likely represent a brisk walk for most participants. The exercise can be done either outside or on an indoor treadmill. The exercise sessions can be completed on any day of the week but participants will be asked to take at least one rest day between sessions. Participants will be asked to perform at least two out of three of the weekly sessions at the time of day stated during randomisation. The exercise intensity will be prescribed based on heart rate and will equate to 95% of LT1 heart rate. Participants will be provided with a Wahoo activity monitor (Wahoo Fitness LLC, Atlanta, Georgia) and will be asked to monitor their heart rate on the phone application during the exercise sessions. The FASTED‐EX group will perform the exercise after an 8 h fast and will ingest a high carbohydrate meal (1 g kg^−1^ body weight) after each session. The FED‐EX group will exercise 90–180 min after the same high carbohydrate meal. Participants will be able to choose the meal from a predetermined list with prescribed portion sizes ensuring the meal is similar to food they would habitually eat. The meal list includes, but is not limited to, a bowl of cereal and semi‐skimmed milk, toast with jam, bagel and low fat cream cheese, and beans on toast. Participants will be emailed every 2 weeks with their energy expenditure and heart rate during the exercise sessions to encourage compliance with the study protocol. If the intensity of exercise in which LT1 is achieved changes from week 1 to week 4, the prescribed heart rate of the exercise sessions will be amended to ensure the same relative intensity of exercise is undertaken throughout the remaining study period.

### Statistical analysis

2.7

Statistical analysis will be performed on Prism 9 version 9.4.1 (GrahPad Software, San Diego, CA, USA). An intention‐to‐treat analysis will be performed on data of all participants who are randomized. Data will be assessed for normal distribution by inspection of residual plots. Difference between groups at weeks 4 and 12 will be assessed by ANCOVA adjusting for stratification factors, sex and baseline measurements for the whole sample (Bland & Altman, 2015). Additional exploratory analysis will be performed adjusting for change in body mass from baseline for the whole sample and subgroup analysis on males and females separately for all outcomes. Differences between sex at weeks 4 and 12 will be assessed by a two‐way ANCOVA. Statistical significance will be defined as *P* ≤ 0.05.

### Sample size

2.8

Our preliminary data (Edinburgh et al., 2020) showed exercise before feeding resulted in a change in LDL‐C concentrations of −0.41 ± 0.51 mmol l^−1^ compared to −0.01 ± 0.046 mmol l^−1^ with exercise after feeding. Using this effect size of *d =* 0.82, 80 participants will provide >95% power at an α‐level of 0.05 with Student's two‐tailed independent *t*‐test. From previous research we expect a dropout rate of approximately 20%. To account for dropouts 100 participants (50 males and 50 females) will be recruited.

